#### Secondary outcome measures.

The secondary outcome measures include the following: (1) The overall cognitive function will be measured using the ADAS-Cog scale, assessed at the12^th^, 24^th^, 36^th^, 48^th^, and 60^th^ weeks; (2) The memory function will be measured using the word recall and word recognition improvement tasks of ADAS-Cog scales at the12^th^, 24^th^, 36^th^, 48^th^, and 60^th^ weeks; (3) The emotional disorders will be measured using the HAMD and HAMA scales [36,37] at the 12^th^, 24^th^, 36^th^, 48^th^, and 60^th^ weeks. The HAMD scale comprises 17 items that measure somatic and affective symptoms of depression, while the HAMA scale comprises 14 items to measure anxiety. Each item of HAMD and HAMA scales is scored for severity on a scale of 0–4, with a higher score reflecting higher symptom severity; and (4) The sleep quality will be measured using the Pittsburgh Sleep Quality Index (PSQI) [38] at the12^th^, 24^th^, 36^th^, 48^th^, and 60^th^ weeks. The questionnaire covers seven components: quality of sleep, the latency of sleep, duration of sleep, the efficiency of sleep, sleep disturbances, use of sleeping drugs, and daytime dysfunction. The PSQI with higher scores indicates the worse sleep quality.

### Safety measurements

Throughout the intervention period, patients will be closely monitored for adverse events (AEs). This includes routine physical examinations and vital sign monitoring for all participants. The research team will implement all necessary measures to prevent potential accidental injuries associated with the study. Should any such injuries occur, the project will cover the related medical expenses. Comprehensive documentation will be maintained for any AEs, including immediate provision of appropriate medical care to affected individuals and a thorough investigation to determine the cause of the events. As acupuncture can potentially cause AEs like bleeding, hematoma, fainting, severe pain, or local infection [39], any serious event will be promptly reported to the ethics committee, and the affected participant will be withdrawn from the study.

### Data management

All original data will be comprehensively and legibly recorded and preserved in case report forms (CRFs), informed consent forms, and inspection reports. Researchers will be responsible for timely and accurate completion of the relevant information within the CRFs. A third-party data manager will oversee the CRFs throughout the study period. To guarantee data privacy and security, all study documents will be stored in a locked office. The Sichuan Provincial Acupuncture Clinical Medicine Research Center reserves the right to inspect study records and monitor the trial’s progress.

### Quality control

Prior to the trial commencement, all project staff will undergo specialized training on the study protocol and standard operating procedures (SOPs). Acupuncturists, who possess the necessary training, will be expected to adhere to a consistent approach regarding acupuncture prescription, needle angle, direction, manipulation, and stimulation. Additionally, to ensure researcher compliance, group meetings will be held twice a month for communication, study updates, and timely response to any challenges or unforeseen issues encountered during the trial.

### Statistical analysis

The data will be processed and analyzed by an independent statistician using IBM SPSS 26.0. An Intention-to-Treat (ITT) analysis approach will be adopted. Sensitivity analysis will use the Per-protocol (PP) analysis method. A two-sided *P-value* < 0.05 will indicate statistical significance. Descriptive statistics for continuous variables will include means and standard deviations (for normally distributed data) or medians and interquartile ranges (otherwise). Categorical variables will be presented as frequencies and percentages. Generalized estimating equations (GEE) will be used to assess the impact of the acupuncture intervention on outcome variables over time at baseline and weeks 12, 24, 48, and 60, with baseline measurement, time, group, and the group-by-time interaction included as covariates, as these factors may influence the efficacy of the acupuncture intervention. Patterns of missingness will be examined, and multiple imputation will be used assuming missing at random, with sensitivity analyses conducted where appropriate.

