**Methods:**

This is a multicenter, single-blinded, randomized controlled trial (RCT) with a long-term follow-up.166 patients diagnosed with aMCI will be randomly divided into acupuncture group (AG) and sham acupuncture group (SA). The intervention will last for 12 weeks (2 sessions per week), follow-up for 48 weeks, and the study will last a total of 60 weeks. The primary outcomes are the changes in the Alzheimer’s Disease Assessment Scale-Cognitive (ADAS-Cog) score from baseline to week 12 and from baseline to week 60. Generalized estimating equations (GEE) will be used to assess the impact of the acupuncture intervention on outcome variables over time at baseline and weeks 12, 24, 48, and 60.

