### Sample size

The Alzheimer’s Disease Assessment Scale-Cognitive (ADAS-Cog) score will serve as the primary index to evaluate cognitive function improvement in patients with MCI. The sample size calculation for this trial was based on our previous study [30] and pilot study, we anticipate an average effect of 3.5 in the acupuncture group and 1.5 in the control group, with a standard deviation of 3.5 between the groups. Using PASS software, we calculated a required sample size of 132 subjects (α = 0.05, 1 − β = 0.90, two-sided). To account for a potential 20% loss to follow-up, we plan to enroll 83 patients in each group, for a total of 166 aMCI patients in the study.

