### Outcomes

#### Primary outcome measures.

Cognitive function will be measured using the ADAS-Cog scale [35]. The primary outcomes will be the changes in the ADAS-Cog score from baseline to week 12 and from baseline to week 60. The ADAS-Cog, comprised of 12 tasks, evaluates various aspects of cognition, including memory, language, praxis (ability to perform actions), orientation, and attention. It is a widely used instrument in dementia research, with lower scores indicating less cognitive impairment.

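### The GEE uses the baseline score both as a response and as a covariate, so the stated baseline adjustment has no effect on the week-12 and week-60 comparisons and some precision is lost

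*Protocol article*

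**What the plan says.** The primary outcomes section fixes two endpoints: "The primary outcomes will be the changes in the ADAS-Cog score from baseline to week 12 and from baseline to week 60". The Statistical analysis section describes a single GEE model, which takes the outcomes "at baseline and weeks 12, 24, 48, and 60, with baseline measurement, time, group, and the group-by-time interaction included as covariates". The Methods paragraph of the abstract repeats the occasions, again with baseline among them: "outcome variables over time at baseline and weeks 12, 24, 48, and 60". The article does not say whether time is categorical or linear, and it does not single out a model term as the primary test.

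The Sample size section gives the design figures. For the expected effects it states "we anticipate an average effect of 3.5 in the acupuncture group and 1.5 in the control group". For the variability it adds "with a standard deviation of 3.5 between the groups", and the error rates are "α = 0.05, 1 − β = 0.90, two-sided". These lead to 132 evaluable and 166 enrolled patients.

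**The concern.** A baseline score can serve in a longitudinal model as the first response or as a covariate for the later responses. Either is sound. Here one sentence gives it both roles. At the baseline occasion the response is the covariate itself, and a contrast of a later visit against baseline, compared between groups, removes anything that is constant within a patient, including that covariate. The article presents the covariates as factors that may affect efficacy, so a reader will expect baseline-adjusted estimates. If the sentence is implemented as written, the reader gets unadjusted change scores. What is at stake is the precision that the baseline ADAS-Cog, already collected, could give to both primary comparisons, and their protection against chance baseline imbalance.

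**Working it through.** **Inputs from the Sample size section.** Difference 3.5 − 1.5 = 2.0 points; SD 3.5; two-sided alpha 0.05; power 0.90; 20% loss. The text does not say what the SD refers to. I read it as the SD of change, which is an assumption. The correlation rho between baseline and a follow-up score is not given, so I use 0.5, 0.7 and 0.8.

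**1. The plan's own figure.** A two-sample t calculation with difference 2.0 and SD 3.5 gives 66 per arm, 132 in total, with power 0.903. Allowing for loss, 66/0.8 = 82.5, rounded up to 83 per arm, 166 in total. Both stated figures reproduce, as an unadjusted comparison of two means.

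**2. Cancellation.** With categorical time, the mean for group g at occasion t is alpha(g,t) + beta × (mean baseline in g). The contrast for a primary outcome is

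[(AG, t) − (AG, 0)] − [(SA, t) − (SA, 0)].

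Within each bracket the term beta × (mean baseline in g) appears once with a plus and once with a minus. It drops out whatever the value of beta. With complete data, what remains is the raw difference in mean change.

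Fitting the model to simulated complete data (66 per arm) confirms this. In one data set the week-12-by-group coefficient was −3.06308 with SE 0.5486, both with and without the baseline covariate, and it equalled the raw difference in mean change. Baseline-adjusted analysis (ANCOVA) of the same data gave −2.952 with SE 0.481. The identity held in all four simulated data sets, two with an independence and two with an exchangeable working correlation. The article plans multiple imputation; each imputed data set is complete, so the identity would hold in each.

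**3. Cost in variance.** Let sigma be the SD of a single score, equal at both occasions. Per patient, the variance of change is 2·sigma²·(1 − rho). The residual variance after baseline adjustment is sigma²·(1 − rho²). The ratio is

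2(1 − rho)/(1 − rho²) = 2/(1 + rho).

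**4. Cost in power.** Unadjusted SE = 3.5 × √(2/66) = 0.609. Adjusted SE = 0.609 × √((1 + rho)/2). Power ≈ Φ(2/SE − 1.96).

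| rho | variance ratio | SE, change | SE, adjusted | power, change | power, adjusted |
|---|---|---|---|---|---|
| 0.5 | 1.33 | 0.609 | 0.528 | 0.91 | 0.97 |
| 0.7 | 1.18 | 0.609 | 0.562 | 0.91 | 0.95 |
| 0.8 | 1.11 | 0.609 | 0.578 | 0.91 | 0.93 |

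Simulations with 66 per arm and compound symmetry agree within about 0.01: about 0.91 for the change contrast, against 0.97, 0.94 and 0.93 to 0.94 with baseline as covariate only.

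**The case against.** The strongest reply is that nothing here invalidates the trial. With categorical time and baseline as reference, the week-12-by-group and week-60-by-group coefficients are exactly the between-group differences in the two primary changes. Randomisation makes them unbiased, and they carry the power that the sample size was built on. The adjusted figures are a bonus, not the repair of a shortfall, and at rho 0.8 the bonus is only two or three percentage points. All of this stands.

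A second reply is that the list of occasions only describes the span of data, with baseline entering solely as the covariate. On that reading nothing cancels. But the sentence places baseline among the occasions at which the outcomes are assessed, on the same footing as the later weeks, and the abstract does the same. At best the wording allows two models that give different estimates.

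A reader might also infer that the primary outcomes will be judged by the joint group-by-time test over all visits, and so are not tested at all. The article does not support that. It says the interaction is in the model, never that its joint test decides the trial. Nor is the absence of a named contrast a fault: the endpoints are fixed in the outcomes section, and linking them to model terms is ordinary content for an analysis plan that is not shown here.

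**Conclusion.** The point holds in a limited form. As written, baseline has two roles in one model, and the stated adjustment does nothing for the contrasts that define the primary outcomes. The result is a valid but less efficient analysis, with variance 11% to 33% above the baseline-adjusted alternative over the assumed rho range of 0.8 to 0.5. A chance baseline difference also stays in the estimate for the particular trial, although it averages out over randomisation.

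The cancellation is exact given categorical time and complete data. The size rests on three assumptions: that 3.5 is the SD of change, that score variances are equal over time, and the chosen values of rho. It should be corrected because the gain uses data already being collected, not because the planned test would mislead.

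**What to change.** Use baseline once. Restrict the response to post-baseline visits and fit categorical time, group, group-by-time and baseline score, optionally with baseline-by-time. State that the two primary comparisons are the model-based group differences at week 12 and at week 60, each with a 95% confidence interval, and not the joint interaction test.

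An equivalent route keeps baseline as a response, drops it as a covariate and constrains the two groups to a common baseline mean. The precision is recovered only if the working correlation links baseline to the later visits. Under an independence structure the constrained model reduces to a comparison of follow-up means, so that choice would have to be stated as well.

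The cost is a change of wording in the article's analysis section and in any analysis plan. No extra data, patients or software are needed. The article schedules recruitment to December 2026 and completion of analysis in June 2027, so the change can be made before the data are analysed.

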## Discussion

To explore the effective intervention measures of aMCI is one of the current research hotspots. Acupuncture has been widely used in non-drug therapies for various types of cognitive dysfunction, including MCI [40], postoperative cognitive impairment [41], post-stroke cognitive impairment [42], and vascular cognitive impairment [43], etc. The mechanism of acupuncture improving cognitive function may be related to enhancing hippocampal synaptic transmission, inhibiting neuroinflammation, regulating neurotransmitter levels, and alleviating oxidative stress [44–47]. Yang W et al.‘s bibliometric review suggested that acupuncture treatment of MCI can improve cognitive function [19]. A systematic review demonstrated that acupuncture appears effective for aMCI when used as an alternative or adjunctive treatment [48]. However, the study also suggested that more rigorously designed studies are needed to further verify this conclusion. According to our earlier preliminary clinical trial of acupuncture intervention in patients with aMCI, it was found that acupuncture has lasting but unclearly sustained positive effects. Since aMCI is a chronic disease that requires long-term observation, we will continue a long-term follow-up of 60 weeks in this trial to assess the sustained efficacy of acupuncture intervention.

Based on a network meta-analysis of diverse acupuncture interventions for MCI [22] manual acupuncture appears to be one of the most effective approaches. In this trial, we will employ manual acupuncture. The needles will be manipulated manually every 10 minutes to maintain the *deqi* sensation. Five acupoints will be selected for treatment: Taixi (KI 3), Dazhong (KI 4), Sanyinjiao (SP 6), Shenting (GV 24), and Baihui (GV 20). Studies suggest that KI 3 acupoint stimulation may enhance cerebral neuron activity in MCI patients [49,50]. Q Zhang et al. [51]. revealed that KI 4 is associated with influencing executive functions, emotional responses, and social behavior. SP 6 is a frequently used acupoint for various cognitive disorders [52]. Moreover, a data mining study has shown that SP6 is the core acupuncture point for acupuncture treatment of AD [53]. GV 24 and GV 20, located on the head and belonging to the governor meridian, play a vital role in influencing brain function, including cognition [22]. An animal experimental study found that electroacupuncture stimulation of GV 20 and GV 24 in mouse models can inhibit neuroinflammatory responses to prevent cognitive decline [54].

ADAS-Cog is a brief assessment instrument focused on multiple cognitive domains [55]. Previous studies support the use of ADAS-Cog in predicting the conversion to AD in aMCI population [56], and highlight its clinical utility in detecting those with aMCI [57,58]. Moreover, ADAS-Cog has been widely used as an outcome measure to assess therapeutic effect [59–61]. Over the years, anxiety and depression have been identified as risk factors for progression from aMCI to AD dementia [62]. It is now understood that depression, affecting approximately 52% of AD patients, can further exacerbate cognitive decline and increase mortality and suicide risk [63]. Furthermore, sleep plays a critical role in healthy cognition, including memory formation [64]. Sleep disorders may serve as both a potential risk factor for AD and worsen its pathological progression [65]. To comprehensively evaluate acupuncture’s effectiveness, we will explore its impact on cognitive function, emotional state, and sleep quality. The ADAS-Cog, HAMD, HAMA, and PSQI scales will be used to assess overall treatment outcomes. The control group will receive sham acupuncture. While debates persist about acupuncture’s effectiveness, with some attributing it to the placebo effect or arguing that sham acupuncture may not be entirely inert [66,67], this trial will implement rigorous blinding. Patients, researchers involved in recruitment, evaluation, and data analysis will remain unaware of group assignments, enhancing concealment and minimizing potential bias.

We acknowledge certain limitations within our trial. Firstly, acupuncture can cause mild pain and skin irritation. This discomfort may deter aMCI patients from consenting to treatment and completing the full course of the study. Secondly, due to the nature of the intervention, acupuncturists cannot be blinded to treatment allocation and potential effects. To minimize bias, acupuncturists will be instructed to avoid discussing treatment specifics with patients. Finally, due to the limitations of manpower and resources at present, only a standardized acupuncture will be studied, and further research is needed in the future.

## Conclusion

Overall, this randomized controlled trial will evaluate the long-term effect of acupuncture for treating patients with aMCI. This study aims to provide valuable insights and clinical guidance for the management of aMCI.
